## **Background**

Video-assisted thoracoscopic surgery (VATS) has become the primary surgical approach in thoracic surgery. Compared with thoracotomy, VATS is notable for less trauma, lower postoperative pain levels, better quality of life, shorter length of hospitalization, and lower complication rates. Despite numerous analgesic strategies in clinical practice, including thoracic epidural analgesia, paravertebral block, and patient-controlled analgesia, acute postoperative pain still exists after VATS.

Acute postoperative pain is closely related to operation time, chest tube duration, and postoperative activities. After surgery, doctors will encourage patients to cough to promote the expulsion of respiratory secretions, but patients may be afraid to cough forcefully due to postoperative acute pain. About 59% of patients experienced moderate to severe acute pain during the first three days after VATS. In contrast, postoperative pain when coughing is often more severe than when resting. Approximately 51.7% of patients experienced moderate to severe pain when coughing within the first 24 hours after surgery. On postoperative day 7, around 20% of patients were still encountering moderate and severe pain while coughing.

Notably, inadequate management of acute postoperative pain frequently results in chronic post-surgical pain (CPSP). About 43.99% of patients reported CPSP after VATS, and the incidence of moderate or severe chronic

pain is 14.71% among them. CPSP will reduce the quality of life of patients and affect their physical and mental health. The efficacy of drug treatment is limited for CPSP at present. Acute postoperative pain control and prevention of CPSP still lack effective interventions.

Due to its significant analgesic effect, electroacupuncture (EA) has been widely used to alleviate various clinical pains such as knee osteoarthritis, acute renal colic, and low back pain. A previous clinical trial on managing postoperative pain through acupuncture following thoracoscopic pulmonary resection found that the numerical rating scale (NRS) scores at 24h, 48h, and 3 months after surgery in the EA group were lower than those in the sham acupuncture group. The total pressing numbers of patient-controlled intravenous analgesia (PCIA) also showed the same result. EA might be efficacious in alleviating acute postoperative pain following VATS, but many shortcomings in existing clinical studies, such as small amount of research, small sample size, low research quality and so on. Therefore, we designed this randomized controlled trial to observe whether EA combined with standard care can alleviate the acute pain of patients with non-small cell lung cancer (NSCLC) after VATS compared with sham electroacupuncture (SA).

## **Objectives**

This trial aims to assess the feasibility and efficacy of EA with standard care versus SA with standard care for acute postoperative pain after VATS.

Hypothesis testing:

H0: Efficacy of EA = Efficacy of SA

H1: Efficacy of EA  $\neq$  Efficacy of SA

## Study design

This trial is a multi-center, randomized, sham controlled acupuncture clinical trial that follows the CONSORT and the STRICTA. Fig 1 shows the flow diagram of the trial. Fig 2 shows the visiting time point.

[figure not shown]

Fig 1. Study flow diagram.

[figure not shown]

Fig 2. Visiting time point.

## Participants

The participants are patients with NSCLC who undergo VATS in two hospitals. The two hospitals are as follows:

- ① The First Affiliated Hospital of Zhengzhou University
- ② Cancer Hospital Chinese Academy of Medical Sciences

Participants will be recruited through wards.

Diagnostic criteria: Patients diagnosed as NSCLC by pathology.

## Inclusion criteria:

1. Men or women aged 18 to 75 years
2. Patients diagnosed with NSCLC before or during surgery
3. Undergoing VATS for pulmonary resection (including lung wedge resection, segmentectomy, and pulmonary lobectomy) for the first time
4. American Society of Anesthesiologists physical status I or II 筛选表加
5. Having no communication barriers and can cooperate with 3 months telephone follow-up

## 6. Willing to sign informed consent

### **Exclusion criteria:**

1. Patients with a history of previous chest surgery (e.g., mastectomy, thoracotomy, or thoracoscopic surgery), or chronic pain
2. Patients with a history of alcohol abuse or drug misuse
3. Patients with a history of preoperative respiratory infection, chronic cough, sputum production, or postnasal drip syndrome
4. Having received chemotherapy, radiation therapy, or acupuncture treatment within 3 months prior to the trial
5. Conversion to open surgery or require postoperative admission to the Intensive Care Unit
6. Patients who are allergic to analgesic drugs and unwilling to use patient-controlled intravenous analgesia (PCIA) after surgery
7. Planning to receive additional surgeries within 3 months postoperatively
8. Having neurological illnesses, pregnancy, lactation, severe hypertension, diabetes, cardiovascular disease, serious hepatic or renal insufficiency, or infectious diseases
9. Having metal allergy, coagulation abnormalities, infections at the selected acupoint sites, or the presence of implantable medical devices such as pacemakers
10. Participating in other clinical trials

Those who meet one or more of the above requirements will be excluded.

## **Randomization**

Stratified block randomization will be applied with stratification according to the two research centers and variable block lengths. Sixty eligible patients will be randomly assigned to the EA or SA group in a 1:1 ratio. A statistician not involved in the implementation or statistical analysis of the trial will generate the random sequences using the STATA statistical software (version 12.0; StataCorp LP). The random number is kept by the independent administrator, who does not participate in the trial intervention, evaluation, and statistics. The CRC will contact an independent administrator by phone to obtain randomization information.

## **Blinding**

Patients, outcome assessors, and the statistician will be blinded to group assignments to reduce potential bias. The acupuncturist is responsible for the acupuncture operation and using an EA apparatus. The appearance of the EA apparatus in the two groups will be identical, but the internal wires of the EA apparatus in the SA group will be cut to inhibit normal operation. Due to the characteristics of the acupuncture, acupuncturists will not be masked.

## Procedure

### 1. conventional therapy

All the patients will be scheduled for surgery in the morning and will undergo general anesthesia during the surgery. All patients will receive PCIA for postoperative pain management. The analgesic solution, containing 14 mg of hydromorphone, 0.15 mg of palonosetron, and 100 mg of flurbiprofen axetil, will be diluted with normal saline to 200 mL (background dose, 3 mL h; bolus, 4mL; and interval, 15 min). If the numeric rating scale (NRS) pain score at rest is  $\geq 4$  after 2 consecutive PCIA, additional dezocine will be administered intravenously as rescue medication (Intravenous injection, 5 mg/ time, no more than 120 mg/ day at most, and the interval between two doses is not less than 2 h).

### 2. Interventions

Patients will receive four sessions of EA or SA within 72 h after surgery (treatment timepoint 1: upon patients return to the ward, treatment timepoint 2: 6 h after surgery, treatment timepoint 3: at 2 pm on postoperative day 1, and treatment timepoint 4: at 2 pm on postoperative day 2). Each treatment will continue for 30 minutes.

#### (1) Electroacupuncture group

Acupoints: the bilateral *Taichong* (LR3), *Yanglingquan* (GB34), *Kongzui* (LU6), *Neiguan* (PC6), *Hegu*(LI4), and *Neimadian* (Extra point).(Table 1)

Needles: Single-use sterile acupuncture needles with 0.25 mm × 40 mm

and 0.40 mm × 50 mm.

Operation: After the acupuncture site and the acupuncturist's hand are strictly disinfected with 75% alcohol, the acupuncturist holds needles of in his right hand. LR3, GB34, LU6, PC6, and LI4 will be inserted with needles of 0.25 mm × 40 mm. *Neimadian* will be inserted with needles of 0.40 mm × 50 mm. There is manipulation for *de qi* (*Neimadian*: the first toe dorsiflexion, and other toes flexion, and other acupoints have a sensation combining sourness, numbness, distention, and heaviness) at each acupoint. Electric stimulation will be used for 30 minutes with an EA apparatus. The paired electrodes of the EA apparatus will be attached to the needle handles at GB34 and *Neimadian*. Continuous waves at a frequency of 2 Hz will be set, gradually increasing the electric current to a tolerable level for the patient.

**Table 1 Location of acupoints for EA group**

| Acupoints                    | Locations a                                                                                                                                              | Angle              | Depth     |
|------------------------------|---------------------------------------------------------------------------------------------------------------------------------------------------------------------|--------------------|-----------|
| Taichong (LR3) | On the dorsum of the foot, between the first and second metatarsal bones, in the depression distal to the junction of the bases of the two bones, over the dorsalis | straight
insert | 0.5-1 cun |

|                                          |                                                                                                                                                            |  |           |
|------------------------------------------|------------------------------------------------------------------------------------------------------------------------------------------------------------|--|-----------|
|                                          | pedis artery                                                                                                                                               |  |           |
| Yanglingquan
(GB34)     | On the fibular aspect of the leg, in the depression anterior and distal to the head of the fibula                                                          |  | 1-1.5 cun |
| Kongzui (LU6)              | On the anterolateral aspect of the forearm, on the line connecting LU5 with LU9, 7 cun superior to the palmar wrist crease                                 |  | 0.5-1 cun |
| Neiguan (PC6)              | On the anterior aspect of the forearm, between the tendons of the palmaris longus and the flexor carpi radialis, 2 cun proximal to the palmar wrist crease |  | 0.5-1 cun |
| Hegu (LI4)                 | On the dorsum of the hand, radial to the midpoint of the second metacarpal bone                                                                            |  | 0.5-1 cun |
| Neimadian
(Extra point) | On the medial side of the lower leg, 7 cun above the medial malleolus and 0.5 cun                                                                          |  | 0.5-1 cun |

|  |                             |  |  |
|--|-----------------------------|--|--|
|  | from post edge of the tibia |  |  |
|--|-----------------------------|--|--|

## (2) Sham electroacupuncture group

Acupoints: Six non-acupoints.

Needles: Single-use sterile acupuncture needles with 0.25 mm × 25 mm and 0.40 mm × 25 mm.

Operation: After the acupuncture site and the acupuncturist's hands are strictly disinfected with 75% alcohol. The needling depth will be 2-3 mm. There will be no manipulation to reach *de qi* at any non-acupoint. The appearance of the EA apparatus will be identical in both groups. However, the internal wires of the EA apparatus will be cut in the SA group. Hence, no electric current will be delivered while the apparatus will be turned on. Electric stimulation will be used for 30 minutes with an EA apparatus.

**Table 2 Location of non-acupoints for SA group**

| Non-Acupoints  | Locations                                                                                                                   |
|----------------|-----------------------------------------------------------------------------------------------------------------------------|
| Non-Acupoint 1 | 2 cun above the medial malleolus (between the liver and spleen meridian)                                                    |
| Non-Acupoint 2 | In the middle of Yanglingquan (GB34) and Zusanli (ST36) points (between the gallbladder and stomach meridian) |
| Non-Acupoint 3 | on the ulnar side of the arm, half way between the epicondylus medialis of the humerus and the                              |

|                |                                                                      |
|----------------|----------------------------------------------------------------------|
|                | ulnar side of the wrist                                              |
| Non-Acupoint 4 | Half way between the tip of the elbow and the axilla                 |
| Non-Acupoint 5 | On the front arm of deltoid muscle and biceps brachi junction        |
| Non-Acupoint 6 | 2 cun above Sanyinjiao (SP6), between the liver and spleen meridian) |

If the subjects take drugs unrelated to analgesia, it is also necessary to record the reasons for taking drugs, the name of the drugs, the mode and dosage of drugs, and the time of taking drugs and stopping drugs.

## **Outcomes**

### **Primary outcome**

The average postoperative pain score during coughing is recorded using NRS within 72 h after surgery.

NRS scale is an effective tool to evaluate pain, with high reliability and validity, easy to record, and widely used. The scale requires patients to rate themselves according to the degree on a 10-point scale, which is divided into 1-10 grades. According to the corresponding figures, the pain can be divided into different degrees, and the middle from 0-10 represents the pain of different degrees that gradually increases. 0 is no pain, 1-3 is mild pain, 4-6 is moderate pain, and 7-10 is severe pain.

## **Secondary outcomes**

- (1) The average pain score during rest, coughing, and mobilization (moving from the lying to the sitting position) will be measured by NRS (assessment time: 24h, 48h, and 72h after VATS).
- (2) Pain scores during rest and the incidence of CPSP (defined as NRS  $\geq 1$ ) at month 3 after surgery.
- (3) Five-level EuroQol five-dimensional questionnaire (EQ-5D-5L) (assessment time: before surgery and at 24h, 72h, and month 3 after surgery).
- (4) The severity of postoperative cough measured by cough symptom score (assessment time: month 1 and month 3 after surgery).
- (5) The dosage of postoperative analgesic drugs and rescue medication. (assessment time: the whole study period).
- (6) The postoperative pulmonary complications (atelectasis, pulmonary infection, pleural effusion, pneumothorax, etc.) and adverse events of acupuncture and drugs (assessment time: the whole study period).
- (7) First expectorated sputum (assessment time: the whole study period).
- (8) Chest tube duration (assessment time: the whole study period).
- (9) Length of postoperative hospital stay (assessment time: the whole study period).
- (10) Blinding assessment (assessment time: after the second treatment).

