## **Sample size calculation**

Based on previous studies, the average postoperative pain score during coughing for the EA and SA groups is estimated to be  $3.0 \pm 1.7$  and  $4.4 \pm 1.7$ . To achieve a statistical power of 80% with a two-sided significance level of 5%, 24 patients per group are required. Sixty patients (30 per group) are required, accounting for a dropout rate of 20%. This pilot trial is intended to establish initial data for the primary outcome measure, and the results will be used to calculate the sample size for the next larger randomized controlled trial.

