## **Statistical analysis**

Statistical analysis will be processed using SPSS Statistics 27. Measurement data will be described as mean  $\pm$  standard deviations ( $M \pm SD$ ), median, or interquartile range. Categorical data will be presented by frequency, percentage, or constituent ratio. Independent t-test or

Wilcoxon rank-sum test will be used to compare the measurement data between groups. The chi-squared test or Wilcoxon rank-sum test will be used to compare the categorical data between groups. The significant level is  $P < 0.05$ , which is considered to be statistically significant.

All randomly assigned patients will be included in the intention-to-treat (ITT) analysis. The per-protocol (PP) analysis, which includes participants completing 80% of the treatment without major protocol deviations or omissions will be used for the primary outcome as sensitivity analysis.

Normally distributed continuous variables will be analyzed using independent t-test. Skewed continuous variables will be analyzed using Wilcoxon rank-sum test. Categorical data will be analyzed using the chi-squared test or Wilcoxon rank-sum test. We will perform a predefined subgroup analysis on primary endpoints according to the chest tube duration, the number of incisions, etc.

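### EQ-5D-5L is measured before surgery, but the stated analysis makes no baseline adjustment: valid, yet less precise than it could be, by an amount the protocol does not allow one to fix

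*Protocol*

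**What the plan says.** Protocol, Secondary outcomes, item (3), sets the schedule: "Five-level EuroQol five-dimensional questionnaire (EQ-5D-5L) (assessment time: before surgery and at 24h, 72h, and month 3 after surgery". No other primary or secondary outcome has a stated pre-surgery measurement.

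Protocol, Statistical analysis, gives the between-group method for continuous data twice. The first statement offers an independent t-test or a rank test: "Wilcoxon rank-sum test will be used to compare the measurement data between groups". The second splits the choice by distribution: "Normally distributed continuous variables will be analyzed using independent t-test" and "Skewed continuous variables will be analyzed using Wilcoxon rank-sum test". The section does not mention EQ-5D-5L by name. For no outcome does it name a covariate, a regression or mixed model, or a change score.

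Protocol, Randomization, gives the size and allocation: "Sixty eligible patients will be randomly assigned to the EA or SA group in a 1:1 ratio". The only stratification factor is research centre.

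**The concern.** One generic rule, suited to outcomes without a baseline, also covers the one outcome that has one. A two-sample test on follow-up scores ignores the pre-surgery score. A two-sample test on changes uses it, but with a coefficient fixed at 1 instead of one estimated from the data. Both leave in the error term some variation that the pre-surgery score could explain.

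What is at stake is the width of the confidence intervals for the quality-of-life difference at 24 h, 72 h and month 3. With 30 patients per arm those intervals will be wide in any case, so avoidable noise is worth removing if the baseline is predictive.

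**Working it through.** **The plan's own figure.** The protocol has no calculation for EQ-5D-5L. Its one sample-size figure concerns the cough pain score, with means 3.0 and 4.4 and SD 1.7: "To achieve a statistical power of 80% with a two-sided significance level of 5%, 24 patients per group are required". By the normal approximation, n = 2 × (1.960 + 0.842)² × (1.7/1.4)² = 2 × 7.849 × 1.4745 = 23.1, which rounds up to 24. Allowing for 20% dropout, 24/0.80 = 30 per arm, 60 in all. The figure reproduces, and this point does not affect it.

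**Inputs for EQ-5D-5L.** 30 per arm comes from the protocol, falling to 24 if the allowed 20% drop out. The correlation r between pre-surgery and follow-up score is not in the protocol; 0.1, 0.2, 0.3 and 0.5 are assumed values.

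**Formulas**, relative to a t-test on follow-up scores (variance factor 1):
- ANCOVA on baseline: variance factor 1 − r².
- Equivalent unadjusted size: 30/(1 − r²) per arm.
- Difference detectable with 80% power at 30 per arm: 0.736 SD unadjusted, multiplied by √(1 − r²).
- t-test on change scores, equal SDs before and after: variance factor 2(1 − r).

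| r (assumed) | 1 − r² | Variance removed | Equivalent per arm (from 30) | Equivalent per arm (from 24) | Detectable difference, SD | Change-score factor |
|---|---|---|---|---|---|---|
| 0.1 | 0.99 | 1% | 30.3 | 24.2 | 0.732 | 1.8 |
| 0.2 | 0.96 | 4% | 31.2 | 25.0 | 0.721 | 1.6 |
| 0.3 | 0.91 | 9% | 33.0 | 26.4 | 0.702 | 1.4 |
| 0.5 | 0.75 | 25% | 40.0 | 32.0 | 0.637 | 1.0 |

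**Change scores against ANCOVA.** 2(1 − r) − (1 − r²) = (1 − r)², which is positive for every r below 1. The change score is therefore less efficient than ANCOVA, and below r = 0.5 it is also worse than ignoring the baseline.

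**Cost of estimating the baseline slope.** The table leaves this out. With a roughly normal baseline and N = 60, it raises the expected variance by a factor of about 1 + 1/(N − 4) = 1 + 1/56 = 1.018. At r = 0.1 the net factor is 0.99 × 1.018 = 1.008, so there is no gain. At r = 0.2 it is 0.96 × 1.018 = 0.977, and at r = 0.5 it is 0.75 × 1.018 = 0.764.

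**Chance imbalance is the same quantity.** The standard error of the baseline difference between arms is √(2/30) = 0.258 SD. Carried into the follow-up comparison it is r × 0.258, or 0.077 SD at r = 0.3 and 0.129 SD at r = 0.5. Its square, r² × 2/30, is exactly the variance that ANCOVA removes. It must not be added to the gain in the table.

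**The case against.** Four arguments weigh against the point.

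**It belongs in the analysis plan.** How one of ten secondary outcomes is adjusted is often left to a SAP, which is not shown here. That would settle the matter if the protocol were silent. But it names the tests for continuous data twice and without exception, so a SAP using ANCOVA would depart from it. The objection lowers the importance of the point but does not remove it.

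**Nothing stated is wrong.** This stands. A reader might infer that leaving out the baseline biases the comparison, or lets a chance imbalance pass for a treatment effect more often than the 5% level allows. The protocol does not support that. Under randomization the unadjusted comparison is unbiased, and its standard error already allows for chance imbalance.

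**The protocol does not say that raw follow-up values are compared.** This also stands. A reader might take the t-test rule to mean so, but changes from baseline are not excluded. The point survives because neither version is as efficient as baseline adjustment.

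**The correlation may be low.** Entry is limited to ASA I–II, and chronic pain, chronic cough, diabetes and cardiovascular disease are among the exclusions. Pre-surgery scores may therefore vary little, and scores at 24 h and 72 h may depend mostly on the operation. Values of r near 0.1–0.2 are plausible, and the gain would then be negligible. Nothing in the protocol rules this out.

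**Conclusion.** The point holds as one of precision. The protocol collects a baseline for EQ-5D-5L, fixes two-sample tests without adjustment, and leaves open whether follow-up values or changes are compared. The size cannot be stated as a single figure. It runs from nothing useful at r = 0.1, through 9% of residual variance at r = 0.3, to 25% at r = 0.5. These are assumed correlations, and the ANCOVA figures rest on a linear relation with similar slopes in the two arms.

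The importance is modest. EQ-5D-5L is a secondary outcome in what the Sample size calculation section calls a pilot trial, and neither the primary outcome nor the 60 patients depend on it. The change is a nearly costless improvement, not the repair of an invalid analysis.

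**What to change.** Add to the Statistical analysis section, before unblinding, a sentence specific to EQ-5D-5L:

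- Compare the groups at 24 h, 72 h and month 3 by ANCOVA, or by one mixed model over the three times, with the pre-surgery score and centre as covariates. Centre is included because the randomization is stratified by it.
- Report adjusted mean differences with 95% confidence intervals.
- If scores are skewed, keep the rank-sum test, or a rank-based ANCOVA, as a sensitivity analysis, and state whether the rank-sum test is applied to follow-up values or to changes.

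The cost is protocol or SAP wording and two degrees of freedom (58 to 56 in the ANCOVA at a single time with all 60 patients). No new data, visits or patients are needed.

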### **Termination standard**

- ① The patient has serious adverse events, and the clinical trial of this case needs to be stopped according to the doctor's judgment.
- ② If other diseases affect the observation of the trial, the clinical trial should be stopped according to the doctor's judgment, and the case should be treated as invalid.
- ③ There are important deviations in the implementation of the clinical study protocol, such as poor compliance, which makes it difficult to

evaluate the efficacy of acupuncture.

- ④ The subject is unwilling to continue the clinical trial during the clinical trial and asks the competent doctor to withdraw from the clinical trial.

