## **Risk and Management**

### **Acupuncture Risk**

Evaluation of adverse events at any time in the process of acupuncture includes hematoma, fainting, continuous post-needling pain, etc.

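### Outside the lung, the safety outcome counts only adverse events attributed to acupuncture or drugs, so the comparison between arms depends on a causal judgement that the randomised sham design does not need

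*Protocol*

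**What the plan says.** The safety outcome is item (6) of the Protocol's Secondary outcomes. It has two parts.

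- The first is "The postoperative pulmonary complications (atelectasis, pulmonary infection, pleural effusion, pneumothorax, etc".), an open list that needs no view on cause.
- The second is "adverse events of acupuncture and drugs (assessment time: the whole study period"), which names two causes.

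Three other places bear on the point.

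- Under Termination standard, serious adverse events appear without any limit on cause, but only as a reason to stop a patient's participation: "The patient has serious adverse events, and the clinical trial of this case needs to be stopped according to the doctor's judgment".
- Under Acupuncture Risk, the Protocol says "Evaluation of adverse events at any time in the process of acupuncture includes hematoma, fainting, continuous post-needling pain, etc".
- Under Blinding, patients, outcome assessors and the statistician are masked, while "acupuncturists will not be masked".

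On timing, "Patients will receive four sessions of EA or SA within 72 h after surgery", each lasting 30 minutes. Follow-up runs to month 3, and the inclusion criteria require patients who can be reached by telephone for that long.

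**The concern.** Every patient has a lung resection under general anaesthesia and then receives PCIA with an opioid, an antiemetic and a non-steroidal anti-inflammatory drug, with a further opioid as rescue. In that setting a bleed, an arrhythmia, dizziness or a swollen limb may plausibly come from surgery, from a drug, from needling or from prior disease. Under item (6), the first three of these events to be labelled surgical would simply not be counted, and the same would hold for any other non-pulmonary event so labelled.

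Two things are at stake. Events can be lost, which matters when each arm has only 30 patients. The loss can also differ between arms if beliefs about what real or sham needling can cause influence the label. Randomisation against a sham control already permits a comparison of all events that needs no such belief, and the outcome definition gives that up. An analysis plan cannot repair this later if events outside the definition were never collected. Because the Protocol describes the trial as a pilot for a larger one, the definition may also be carried forward.

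**Working it through.** **Scope, by setting the sections side by side**

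| Type of event | Counted under item (6)? | Causal judgement needed? |
|---|---|---|
| Pulmonary complication | Yes | No |
| Non-pulmonary, attributed to acupuncture | Yes | Yes |
| Non-pulmonary, attributed to a drug | Yes | Yes |
| Non-pulmonary, attributed to surgery or underlying disease | No | Yes |
| Serious event of any cause | Only if it falls in one of the first three rows; otherwise it is only a possible reason to stop participation | As in its row |

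The gap is the fourth row. An event moved between needling and drugs stays in the count. Only a move to surgery or underlying disease removes it.

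**Size of the possible loss**

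The Protocol gives no adverse event rate and no planned safety figure, so there is nothing of its own to reproduce. The inputs are:

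- n = 30 per arm (Protocol, Sample size calculation);
- true event rate p, assumed;
- share d of those events set aside as surgical, assumed.

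The rate that is counted is p(1 − d), and the chance of at least one counted case in an arm is 1 − [1 − p(1 − d)]^30.

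With p = 5%:

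- d = 0: 1 − 0.95^30 = 0.785
- d = 0.5: 0.05 × 0.5 = 0.025, and 1 − 0.975^30 = 0.532

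Over a range of assumptions:

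| True rate p | d = 0 | d = 0.25 | d = 0.5 | d = 0.75 |
|---|---|---|---|---|
| 1% | 26% | 20% | 14% | 7% |
| 5% | 79% | 68% | 53% | 31% |
| 10% | 96% | 90% | 79% | 53% |

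At p = 5% the expected number of cases in an arm is 30 × 0.05 = 1.5 if all are counted, and 30 × 0.025 = 0.75 if half are set aside.

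**Timing wording**

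Item (6) sets its window as the entire study. The Acupuncture Risk section speaks of the process of acupuncture, which could be read as the sessions alone (4 × 30 = 120 minutes). That section does not limit itself to the sessions, and it lists pain that continues after needling. The two phrases differ, but the second does not override the first.

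**The case against.** Four objections deserve an answer.

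1. *Timing.* A reader might infer from the Acupuncture Risk section that events are evaluated only while needles are in, so that later ones are missed. The documents do not support this. The section contains no such restriction, it introduces the management of acupuncture events, its list is open and includes persistent post-needling pain, and the outcome window in item (6) is the whole study. What remains is a phrase to align.

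2. *Who attributes.* A reader might also infer that staff who know the arm decide the cause. The acupuncturists are unmasked, but no section gives them the recording or attribution of events, and the outcome assessors are blinded. Quality control refers to standard operating procedures for each step, which are not shown. A bias that favours one arm is therefore possible but not shown.

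3. *Transfers between needling and drugs.* It is tempting to argue that dizziness or nausea blamed on needling in one arm and on PCIA in the other would create a false difference. In the outcome as stated it would not, since both causes are counted. Such a difference would appear only if acupuncture-attributed events were compared alone, and the Protocol states no such comparison.

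4. *Importance.* The objectives are feasibility and efficacy, and no formal safety test is planned. This objection stands and lowers the severity.

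None of the four removes the central point. As written, a non-pulmonary event judged surgical is not an outcome.

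**Conclusion.** The point holds as a limited one. For everything outside the lung, item (6) makes entry into the safety comparison depend on cause, and the Protocol does not say who judges cause. The definition itself is fixed in the Protocol, so this is more than a detail left to an analysis plan.

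The direction and size of any bias between arms cannot be determined from the document. The fall from 79% to 53% in the chance of seeing a 5% event in an arm rests on an assumed rate and an assumed loss of one half. It shows scale and does not estimate what will happen.

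This is a cheap improvement of low severity, because the trial is a pilot and its safety comparison is descriptive.

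**What to change.** In item (6) of Secondary outcomes, keep the pulmonary complications and replace the second part with: *all adverse events, whatever the presumed cause, from randomisation to month 3*. Starting at randomisation, and not at the first session, covers randomised patients who receive no session, in line with the intention-to-treat population in Statistical analysis.

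Have the blinded outcome assessors ask about events at the contacts that the Secondary outcomes already schedule: 24, 48 and 72 h, and months 1 and 3. Tabulate all-cause events by arm as the main safety summary, and report attribution to acupuncture, drugs or surgery only as description.

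As a secondary edit, reword the Acupuncture Risk section so that its evaluation period matches the whole study period in item (6).

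The cost is a wording change and one question at existing contacts. No visit or patient is added. The drawback is a longer event list, much of it related to surgery.
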